So far, there is preliminary evidence supporting the efficacy of MCT for OCD. The clinical significance of treatment effects in the following mentioned studies is calculated using the standard criteria developed by Fisher and Wells [11, 14], based on the method of Jacobson and Truax [21]. Based on these criteria, patients are classified as recovered if they achieved a reduction of minimal 10 points on the Yale-Brown Obsessive Compulsive Scale (Y-BOCS [19]; a semi-structured interview for OCS) and a post-treatment score < 14. When achieving a post-treatment score < 7, patients are classified as asymptomatic. Using single case methodology, Fisher and Wells [12] found clinically significant improvements for four OCD patients with different clinical presentations who were treated individually with MCT. Two of the four participants were asymptomatic at both post-treatment and three-monthfollow-up assessments. Furthermore, Rees and Van Koesveld [33] found that seven out of eight participants in an open trial of group MCT for OCD reached criteria for a recovery status on the Y-BOCS at three-monthfollow-up (87.5%). In an additional study, Fitt and Rees [16] found similar clinically significant reductions among three patients treated with MCT using videoconference. In an open trial of individual metacognitive therapy among 25 patients with OCD, Van der Heiden et al. [39] found statistically significant reductions on all outcome variables. Moreover, in terms of clinically significant results, 74% of the treatment completers (*n* = 19) were classified as recovered after treatment and 47% as asymptomatic. At follow-up, this increased to 80% and 67% respectively. Finally, Simons et al. [35] found positive outcomes of MCT in comparison to ERP in the treatment of pediatric OCD in a case series design. Together, these findings suggest that MCT might be an efficacious treatment for OCD and deserves controlled evaluation. The present trial has been initiated to compare the relative efficacy of MCT with ERP, in an outpatient clinical sample of patients with OCD. Our main hypothesis is that MCT is more efficacious than ERP in the treatment of OCD in terms of both statistically and clinically significant improvements, both directly after treatment (primary outcome) and at follow-up.

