#### Primary outcome

The primary outcome of interest for this MCT superiority study is OCD severity at post-treatment, which will be measured with the Y-BOCS [19], a semi-structured interview and the “gold standard” for measuring OCD symptoms. The Y-BOCS is a clinician-ratedsemi-structured interview designed to rate the severity of both obsessions and compulsion. The Y-BOCS consists of 10 items rated 0–4 (range = 0–40). The Y-BOCS has been shown to have good psychometric properties and is sensitive for measuring treatment effects [40]. Further, good internal consistency for both the subscales (obsessions and compulsions) and for the total score of the Y-BOCS has been reported [18].

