### Statistical analysis

#### Outcomes

Data will be analyzed using SPSS for Windows version 25.

Because of the expected drop-out and the uneven time intervals between measurements (post-test 6-month–30-month follow-up), the use of mixed models is the most appropriate statistical method [36]. This methodology is very suitable to analyze repeated measures by taking dependency between observation into account and the ability to handle missing data. In case of Missing At Random (MAR), we will use these variable(s) as covariate in our analysis. In case of Missing Not At Random (MNAR) we will use pattern mixture models. Mixed models will be adjusted by the baseline values of the repeated measures. Descriptives for means and proportions of baseline clinical and demographic variables between treatment conditions will be reported so potential magnitudes of imbalances can be assessed. Model diagnostics will be assessed by exploring residual plots. In case they are not acceptable, we will apply bootstrapping procedures with the use of R (R core team, 2018).

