Fixed effects in our model will be time, treatment, and their interaction. In case of missingness, we will add these variable(s) also as fixed effects. The Benjamini–Hochberg procedure is applied to the significances of the time*treatment interaction *p*-values (two-sided *p* < 0.05) of the different outcome measures. The time variable will be treated categorically, with the first post-baseline measurement as the reference category. To accommodate the modeling of correlation among repeated measurements, we impose a first order autoregressive (AR (1)) structure on the residuals. Next, the interaction effect between time and group will be explored by analyzing the estimated marginal means at different time points. We expect a significant interaction effect between time and group, which means that scores change differently over time in the two treatment conditions. More specifically, we expect a more negative time trend for MCT than for ERP, indicating that the measurement scores in the MCT condition decline more over time than in the ERP condition. To gain further insight into the statistical significance of the improvements achieved in the two treatment conditions, we will perform a least significant difference test with the estimated marginal means to compare changes between treatment conditions. In accordance with the linear mixed models, we expect a statistically significant decline in both treatment conditions between pretest and post-test, but no statistical differences between post-test and both follow-up measures. To allow for comparison with other studies into the effectiveness of ERP and MCT for OCD, Cohen’s *d* statistic ((mean 1 – mean 2) / pooled SD) will be employed to calculate within-group effect sizes (ES) for changes on outcome measures and to evaluate between-group differences. We will calculate Cohen’s *d* statistics for both intent-to-treat samples by using multilevel analysis with all available data and completer samples (our primary analysis: minimum of eight treatment sessions and no change in medication during treatment will be managed as criteria for each patient to can be classified as treatment completer). Based on previous research, we expect a large within-treatment ES for both treatment conditions (Cohen’s *d* > 0.8). We expect a medium between-group ES in favor of MCT. In addition, the clinical significance of treatment effects and amount of drop-out will be examined also to gain further insight into the clinical value of the two treatment conditions.

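### The plan attaches its only stated significance rule to the time-by-treatment interaction, which does not test the primary question: the MCT–ERP difference in Y-BOCS at post-treatment

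*Protocol article*

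**What the plan says.** **Primary question.** Under Primary outcome: "The primary outcome of interest for this MCT superiority study is OCD severity at post-treatment". The main hypothesis, at the end of the section on metacognitive treatment for OCD, places superiority "both directly after treatment (primary outcome) and at follow-up". The Design section also marks post-treatment as the primary assessment.

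**Model.** Under Statistical analysis, Outcomes: "Mixed models will be adjusted by the baseline values of the repeated measures". The fixed effects are time, treatment and their interaction. On coding: "The time variable will be treated categorically, with the first post-baseline measurement as the reference category". Residuals follow an AR(1) structure.

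**Significance rule.** "The Benjamini–Hochberg procedure is applied to the significances of the time*treatment interaction" p-values of the different outcome measures, with the threshold "two-sided *p* < 0.05". No other test in the section is given a threshold.

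**Expected results.** "We expect a significant interaction effect between time and group, which means that scores change differently over time in the two treatment conditions". A few sentences later the section expects a decline from pretest to post-test in both arms, "but no statistical differences between post-test and both follow-up measures".

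**Follow-up comparisons.** Estimated marginal means at the different time points are to be used to explore the interaction. A least significant difference test on them is offered as additional insight.

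**The concern.** If baseline is a covariate and post-treatment is the reference level of time, the model's terms divide as follows. The treatment coefficient is the baseline-adjusted MCT–ERP difference at post-treatment, which is the primary question. The interaction terms are the changes in that difference from post-treatment to 6 months and to 30 months. The plan puts its significance rule on the second set and none on the first.

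On this reading the two expectations also conflict. If neither arm moves between post-test and follow-up, there is little or no interaction to find, however large the advantage of MCT.

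Two kinds of wrong conclusion are at stake. A durable benefit of MCT would usually give a non-significant result under the stated rule. A significant result could mean that the benefit faded, or that it appeared only later, rather than that MCT was better after treatment.

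**Working it through.** **Inputs from the protocol (Sample size):** d = 0.50, power 0.80, four measurement points, correlation 0.5, drop-out 20%, 50 per arm. Two-sided 0.05 comes from Statistical analysis. **Assumptions:** SD = 1 at every visit; correlation 0.5 taken either as exchangeable or as the lag-one value of an AR(1) pattern over baseline and the three later visits. The AR(1) value is not given in the protocol.

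**1. The plan's own figure.** The Liu–Liang formula for a time-averaged difference is n = 2(z₀.₉₇₅ + z₀.₈₀)²[1 + (m − 1)ρ] / (m d²). With m = 4, ρ = 0.5 and d = 0.5: 2 × 7.849 × 2.5 / (4 × 0.25) = 39.24, so 40 per arm, and 40 / 0.8 = 50. The stated number reproduces. It sizes a difference averaged over four measurements, which is neither the interaction nor the post-treatment contrast.

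**2. Post-treatment contrast, baseline-adjusted.** Residual variance is 1 − 0.5² = 0.75. With 40 per arm, SE = √(2 × 0.75 / 40) = 0.194, and power = Φ(0.5/0.194 − 1.96) = Φ(0.62) = 0.73. With 50 per arm, SE = 0.173 and power = 0.82. Simulation of the baseline-adjusted three-visit model (20,000 trials, AR(1) pattern) gave 0.71 and 0.81.

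**3. Interaction with three levels of time (2 df).** Let δ be the arm differences at post-treatment, 6 and 30 months, Σ the covariance of those visits given baseline, and C the contrasts (6 months − post) and (30 months − post). The Wald test has noncentrality λ = (Cδ)ᵀ[C(2Σ/n)Cᵀ]⁻¹(Cδ). For a constant difference Cδ = 0, so λ = 0 and the rejection rate is 0.05 whatever the size of the difference, n or the correlation. Simulation at d = 0.5 gave 0.052 (40 per arm) and 0.050 (50 per arm).

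For 40 per arm:

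| δ (post / 6 / 30 months) | λ, AR(1) to exchangeable | Interaction rejects | Post-treatment hypothesis |
|---|---|---|---|
| 0.5 / 0.5 / 0.5 | 0 | 5% | MCT better |
| 0.5 / 0.25 / 0 | 3.68 to 5.00 | 39–50% | MCT better |
| 0 / 0 / 0.5 | 5.56 to 6.67 | 55–63% | no difference |

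The last two rows are illustrative profiles, not forecasts in the protocol.

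**4. Interaction with baseline as a fourth level (3 df).** With δ = 0 at baseline and 0.5 at the three later visits, λ = 5.56 (AR(1)) to 7.50 (exchangeable) with 40 per arm, giving power 0.48–0.62. With 50 per arm λ = 6.94 to 9.38, giving power 0.59–0.73.

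**The case against.** The three-level reading is an inference. Nowhere does the protocol say that baseline is left out of time. The sample size counts four measurement points, and the analysis section expects a pretest to post-test decline in line with the mixed models and a steeper downward trend under MCT. All of this fits baseline as a level of time. That stands, and it means one cannot say outright that the interaction cannot detect post-treatment superiority. But this reading does not rescue the rule. Baseline would be both covariate and outcome, the test would be joint over visits, and its power at a constant d = 0.5 stays below 0.80 (step 4).

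The right contrast is also already available: it is the treatment coefficient at the reference visit, and the marginal-mean and least significant difference comparisons can display it. So a reader who infers that a superior MCT would necessarily be declared ineffective goes too far. Only the interaction p-value would be uninformative. Even so, the protocol presents these comparisons as exploration and gives them no threshold of their own.

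The Benjamini–Hochberg step is a correction across outcomes, and the protocol does not call the interaction its primary test. That is true, but no other test has a stated significance rule, and the protocol says that it expects this one to be significant.

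Finally, expecting no statistical differences after post-test is not a claim of identical trajectories. An interaction of exactly zero is the limiting case; the conflict between the two expectations is one of direction and holds on the three-level reading.

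**Conclusion.** The concern holds, conditionally as to its size. Under either reading, the test that carries the significance rule does not answer the question the protocol calls primary. On the natural reading (baseline as covariate, three levels of time) it is blind to any constant MCT–ERP difference, and it can reject when there is no difference at post-treatment. On the alternative reading it has some power, but less than the protocol claims, and it does not isolate post-treatment. The 5% figure is algebraic. The other figures rest on equal variances, complete data on 40 or 50 per arm, and a correlation of 0.5 in an exchangeable or AR(1) pattern. The documents do not support the stronger inference that the plan has no means of showing post-treatment superiority. The estimate is there, and what is missing is its designation as the primary test.

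**What to change.** - Name the baseline-adjusted MCT–ERP difference in Y-BOCS at post-treatment (the treatment coefficient at the reference visit) as the primary test, two-sided 0.05, with a 95% confidence interval.
- Make the 6- and 30-month contrasts secondary, and use the interaction only to describe whether the difference persists.
- State that baseline is a covariate and not a level of time. Take within-arm change from pretest to post-test from a separate descriptive model, and reconcile the stated expectations with this.
- Restate power for the primary contrast: about 0.73 with 40 evaluable per arm and 0.82 with 50, at d = 0.5 and correlation 0.5.

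The primary test uses the data and model already planned. The cost is revised wording, one extra descriptive model, and a stated power that falls somewhat short of 0.80 if 20% drop out. Recruitment was still open when the article was published, with 68 patients randomized.

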## Design and methods

### Design

We will conduct a randomized controlled trial (RCT) with a pretest–post-test (primary outcome) 6-month–30-month follow-up-design. Patients will be recruited from consecutive referrals to the Anxiety Disorders department of PsyQ, an outpatient community mental health center in the Netherlands. After screening for eligibility and informed consent, we will randomize the patients into two groups: MCT and ERP. The number of excluded patients and refusers and their reasons are registered. Participating patients will be assessed by self-report measures and semi-structured clinical interviews administered by a research assistant who is blind to group allocation at entry (pre-treatment), after the last treatment session (post-treatment – primary outcome), six months (first follow-up) after treatment completion and 30 months (second follow-up) after treatment has ended. The latter assessment is included to answer a secondary research questions on the durability of both the ERP and MCT effect on the long term. Due to a lack of studies with follow-up periods of > 1 year [9, 47], the information on longer-term effects are unknown. In case of drop-out, measurements and interviews are also administered directly after treatment had ended whenever this is possible. The study has received ethical approval from the Medical Ethical Committee of the Leiden University Medical Centre (LUMC) (protocol number NL50201.058.14) and is registered in the Dutch Trial Register (protocol number NTR4855). All data will be stored anonymously; there is a data safety and monitoring board for the study. Figure 2 shows a flowchart of the study from patient enrollment up to data analysis and reporting. This study follows the “guidance of standard protocol items: recommendations of interventional study’s (SPIRIT).” The SPIRIT figure template is displayed in Fig. 3. In addition, the SPIRIT checklist can be found in Additional file 1.

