### Sample size

There are no studies available directly comparing ERP with MCT. We chose to design our study with enough statistical power to enable us to detect a medium between-group effect (Cohen’s *d* = 0.5 [6]) from baseline to post-treatment. We chose for this medium between-group effect because expecting a larger difference between the two treatment groups does seem unrealistic since numerous studies have found statistically significant change and large improvements in OCD symptoms after ERP. On the other hand, designing our study to enable us to detect a small between-group effect is of less relevance for clinical practice. We used the statistical method presented by Liu and Liang [22] for sample size calculations for studies with correlated observations. To achieve a power of 0.80 with four measurement points with a correlation of 0.5 between repeated measures (standard value) and to detect a medium effect size (Cohen’s *d* = 0.50) between the two treatment conditions over time on the primary outcome measure, severity of OCD symptoms, and an expected drop-out rate of 20%, the minimal sample size necessary in each condition is 50.

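### AR(1) residuals force equal correlation across the 6-month and 24-month gaps, which can misstate standard errors of change between follow-up visits; the primary post-treatment contrast is not affected with complete data

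*Protocol article*

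**What the plan says.** All references are to the protocol article.

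- **Visits (Design).** After post-treatment, patients are assessed at "six months (first follow-up) after treatment completion and 30 months (second follow-up) after treatment has ended".
- **Reason for mixed models (Statistical analysis, Outcomes).** The section argues that, given drop-out and "the uneven time intervals between measurements (post-test 6-month–30-month follow-up), the use of mixed models is the most appropriate statistical method".
- **Mean model (same section).** "The time variable will be treated categorically, with the first post-baseline measurement as the reference category". Also: "Mixed models will be adjusted by the baseline values of the repeated measures". Together these make baseline a covariate and leave three repeated outcomes.
- **Covariance (same section).** "we impose a first order autoregressive (AR (1)) structure on the residuals". No random effect, time-scaled structure, covariance selection step or robust standard error is stated. Bootstrapping in R is the fallback if residual plots look unacceptable.
- **Planning value (Sample size).** Four measurement points "with a correlation of 0.5 between repeated measures (standard value").

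**The concern.** AR(1) over visits has a single correlation for every adjacent pair and takes no account of elapsed time. Here it requires corr(post, 6 m) = corr(6 m, 30 m) = ρ and corr(post, 30 m) = ρ². One adjacent gap is four times as long as the other. The section itself names the unequal intervals, then fixes a structure that cannot reflect them.

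At stake are the standard errors of change between visits. The plan expects no significant change from post-test to either follow-up, and the 30-month visit was added to answer a secondary question on durability. A standard error that is too large makes the expected absence of change easier to find; one that is too small does the reverse.

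**Working it through.** **1. The plan's own figure.** The article gives no standard error or correlation for the follow-up contrasts, so the only figure to reproduce is the sample size. For a time-averaged difference with one common correlation:

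n = 2(z₀.₉₇₅ + z₀.₈₀)² [1 + (m − 1)ρ] / (m d²), with m = 4, ρ = 0.5, d = 0.5

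= 2 × 7.849 × 2.5 / 1 = 39.24, so 40 per arm; 40 / 0.80 = 50.

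The stated 50 per arm is reproduced. The sizing therefore used an exchangeable correlation. AR(1) with ρ = 0.5 in the same approach gives 32 to 33 evaluable, or 40 to 42 after drop-out.

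**2. What AR(1) converges to.** Assume three visits, equal variances (set to 1), complete data and a large sample. The best-fitting AR(1), in the Kullback-Leibler sense, then has variance 1 and ρ equal to the mean of the two adjacent true correlations: ρ = (r₁ + r₂)/2, where r₁ is post to 6 m and r₂ is 6 m to 30 m.

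**3. Effect on a change contrast.** The variance of a change is proportional to 2(1 − r). Hence:

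- model SE / true SE for either adjacent change: √[(1 − ρ)/(1 − r)]
- for post to 30 m: √[(1 − ρ²)/(1 − r₃)], where r₃ is the true post-to-30-month correlation
- true size of a nominal 0.05 test: 2[1 − Φ(1.96 × ratio)]

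The ratios are the same for change within an arm and for the difference in change between arms.

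**4. Correlation decaying with real time (assumed).** r = r₆^(months/6), so r₁ = r₆, r₂ = r₆⁴, r₃ = r₆⁵. Example with r₆ = 0.5: r₁ = 0.5, r₂ = 0.0625, r₃ = 0.031, ρ = 0.281.

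- post to 6 m: √(0.719/0.5) = 1.20
- 6 m to 30 m: √(0.719/0.9375) = 0.88
- post to 30 m: √(0.921/0.969) = 0.975

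| r₆ | fitted ρ | post–6 m: ratio (size) | 6–30 m: ratio (size) | post–30 m: ratio (size) |
|---|---|---|---|---|
| 0.5 | 0.281 | 1.20 (0.019) | 0.88 (0.086) | 0.975 (0.056) |
| 0.7 | 0.470 | 1.33 (0.009) | 0.835 (0.102) | 0.968 (0.058) |
| 0.9 | 0.778 | 1.49 (0.004) | 0.80 (0.115) | 0.982 (0.054) |

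Adding a stable between-patient share of 0.3 to 0.5 to the true correlation (r₆ = 0.7, AR(1) still fitted alone) leaves the first two ratios at 1.33 and 0.835 and moves post to 30 m to 1.02 to 1.05.

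**5. One common correlation (assumed).** Both adjacent ratios are 1.00. For post to 30 m:

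- residual correlation 0.5: √(0.75/0.5) = 1.22, size 0.016
- residual correlation 0.7: √(0.51/0.3) = 1.30, size 0.011
- if 0.5 is the raw correlation and baseline is adjusted for, the residual correlation is (0.5 − 0.25)/(1 − 0.25) = 0.333: √(0.889/0.667) = 1.15, size 0.024

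**6. Primary timepoint and joint test.** The SE ratio for the between-group difference at post-treatment is 1.00 in every scenario. The simulated size of the joint 2-df time-by-treatment test is 0.056 to 0.062 under real-time decay, 0.043 with a common 0.5 and 0.048 with a common 0.7.

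**The case against.** The strongest reply has four parts.

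- **The primary result is not at risk.** This stands for complete data: the primary outcome is Y-BOCS at post-treatment, and that between-group standard error does not move. A reader might infer that the main comparison is invalid; nothing in the article supports that.
- **The interaction tests are nearly sound.** This also stands. The false discovery rate procedure uses the time-by-treatment p-values, and a reader might conclude that these are wrong. A size of about 0.04 to 0.06 is only a mild departure.
- **A random intercept may be intended.** The article speaks of mixed models and multilevel analysis, and a fuller plan may name one. With a random intercept and an exchangeable truth the fit is exact, and the inflation at 30 months disappears. The two adjacent correlations would still be forced equal, so the spacing problem would remain.
- **The planning correlation need not match the analysis.** This stands too. A reader might call the sizing contradicted, but 0.5 is offered as a standard planning value, the 50 per arm is reproduced, and AR(1) would have required fewer patients.

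Categorical time does handle the spacing for the means, but the covariance remains equal-step. The bootstrap is partial protection at best, because its trigger is residual plots and not a check of the correlation pattern. Deferral to a later analysis plan does not answer the point, since the article states AR(1) outright.

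**Conclusion.** The point holds, mainly for individual contrasts of change between post-treatment visits. The structural mismatch follows directly from the text. Its size and direction do not, because they depend on correlations that the article does not give.

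When correlation decays with elapsed time, the spacing error falls on the two adjacent changes, in opposite directions, and the post-to-30-month contrast is nearly right. The larger error at 30 months needs an exchangeable truth and no random intercept, and is not caused by unequal spacing as such.

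Two further inferences go beyond the evidence. One is that the plan systematically favours finding no change at follow-up: at 30 months the sign depends on the scenario. The other is that the treatment estimates are biased: with complete data the estimated means are unaffected. With missing follow-up data the misfit may reach the estimates, but no missingness scenario has been quantified here.

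All figures assume large samples, equal variances and complete data. The change is worth making because it is cheap and settles the matter whatever the true correlations are.

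**What to change.** In Statistical analysis, Outcomes, replace AR(1) with an unstructured residual covariance for the three post-baseline visits, with small-sample degrees of freedom. Name in advance a fallback for non-convergence, for example heterogeneous compound symmetry.

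The cost is one option in the SPSS syntax and four extra covariance parameters: 3 variances plus 3 correlations, 6 in place of 2. That is feasible with the roughly 80 to 100 patients expected (100 randomised, 20% drop-out). The article reports recruitment still open with 68 randomised, so at that stage the change could be specified before any analysis. The sample size needs no change on this account.

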#### Process measures

Changes in both belief domains that have been proposed to be important in the etiology of OCD are assessed. To study changes in metacognitive beliefs about the meaning, significance, and danger of intrusive thoughts, the Thought Fusion Instrument (TFI [45]) will be employed. To study changes in metacognitive beliefs about the necessity of performing rituals in response to obsessions, the Beliefs About Rituals Inventory (BARI [25]) is used. The TFI consists of 14 items and the BARI of 12 items. All items are answered on a 4-point scale in the range of 1–4. There are few data available about the psychometric properties of the TFI and the BARI. Gwilliam et al. [20] found reasonable internal consistency, a moderate test–retest reliability, and some support for the convergent and divergent validity for the TFI. In the developmental phase of this study, the psychometric properties of the TFI and the BARI will be further assessed by our research group.

The Obsessive Belief Questionnaire (OBQ-44 [29]) is included as another measurement with the purpose of the assessment of beliefs considered to be important in the maintenance of OCD. Factor analysis of the scale reveals four factors: (1) perfectionism and intolerance of uncertainty; (2) importance and control of thoughts; (3) responsibility; and (4) overestimation of treat [28]. The OBQ-44 consists of 44 items answered on a scale of 1–4. The psychometric properties are good.

In addition, on both follow-up assessments, participants will be called by a research assistant, who will ask them to provide responses for the Treatment Change Recording Form (TCRF [38]), which will be used to assess the initiation, termination, or change of any form of therapy, hospital services, support group, self-help program, or medication utilized by the participant since post-treatment.

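### The 30-month visit is there to show durability, but the only stated expectation for change after treatment is a non-significant difference, with no margin or confidence-interval criterion and no stated role for recorded later treatment

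*Protocol article*

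**What the plan says.** Under Design, the protocol article places the second follow-up "30 months (second follow-up) after treatment has ended" and gives its purpose: "secondary research questions on the durability of both the ERP and MCT effect on the long term". The primary outcome is the Y-BOCS at post-treatment, so durability is a secondary matter.

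Under Statistical analysis, Outcomes, the model has time (categorical), treatment and their interaction as fixed effects, with baseline adjustment, variables related to missingness and AR(1) residuals. Estimated marginal means are examined at the time points and compared by least significant difference tests. For change after treatment, the stated expectation is a significant pretest to post-test decline in both arms, "but no statistical differences between post-test and both follow-up measures". Neither that section nor Endpoints gives a margin, an interval criterion or a definition of relapse. The recovery categories under Endpoints are written for the score after treatment.

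Under Process measures, the TCRF is completed at both follow-ups and covers "initiation, termination, or change of any form of therapy, hospital services, support group, self-help program, or medication utilized by the participant since post-treatment". Neither Outcomes nor Endpoints mentions it. The intent-to-treat calculations use all available data.

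**The concern.** Durability is a claim that little has been lost. A non-significant test says only that a loss was not demonstrated, and the smaller the sample, the more easily that happens. If the expected null result is taken as the answer to the durability question, low precision works in favour of the claim.

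Later treatment adds a second difficulty. The article says that OCD tends to be chronic without adequate treatment and that ERP is already usual care at the participating centre. Over 30 months some patients may receive further treatment. Their scores then reflect the randomised treatment plus whatever followed, and a mean built on all available scores does not show how much of the benefit came from each. The information that would help a reader judge this is being collected, but the analysis text does not say how it will be shown.

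**Working it through.** **Inputs.** From Sample size: power 0.80, four measurements, correlation 0.5, d = 0.50, 20% drop-out, 50 per arm. From Outcomes: "two-sided *p* < 0.05", stated for the interaction and assumed here for the sample size and the post-test to follow-up contrasts; also the AR(1) structure. Assumed: the sizes of true worsening, 30 per arm at 30 months as a less favourable case, and the normal approximation throughout.

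**The plan's own figure.** For a between-arm difference averaged over m repeated measures:

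n = 2(1.96 + 0.84)² × [1 + (m − 1)ρ]/m ÷ d² = 2 × 7.85 × (2.5/4) ÷ 0.25 = 39.2, so 40 per arm. With drop-out, 40/0.8 = 50.

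The stated 50 per arm reproduces. It was sized for a between-arm effect of 0.5 SD, not for stability within an arm.

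**Precision of change within an arm.** In SD units, SE = √[2(1 − r)/n].

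- r = 0.5, n = 40: √(1/40) = 0.158; 95% CI half-width 1.96 × 0.158 = 0.31.
- r = 0.25, n = 40: √(1.5/40) = 0.194; half-width 0.38.

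The value 0.25 is 0.5², the AR(1) correlation two visits apart (post-test to 30 months) if adjacent visits correlate at 0.5. Post-test to 6 months is one step, so 0.5 applies there.

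**Chance that a true worsening δ is non-significant**, 1 − Φ(δ/SE − 1.96):

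| n per arm | r | δ = 0.2 SD | δ = 0.3 SD | δ = 0.4 SD |
|---|---|---|---|---|
| 40 | 0.5 | 76% | 52% | 28% |
| 40 | 0.25 | 82% | 66% | 46% |
| 30 (assumed) | 0.5 | 81% | 62% | 41% |
| 30 (assumed) | 0.25 | 86% | 73% | 57% |

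Worked cell (n = 40, r = 0.5, δ = 0.3): 0.3/0.158 = 1.90; 1.90 − 1.96 = −0.06; Φ = 0.475; about 52% non-significant.

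**What the planned size could show.** With a true change of zero, one-sided 0.025 and 80% power, the smallest worsening that can be excluded is (1.96 + 0.84) × SE: 0.44 SD at r = 0.5 and 0.54 SD at r = 0.25. A margin of 0.3 SD would need 88 evaluable per arm (110 after 20% drop-out) at r = 0.5, or 131 (164) at r = 0.25.

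**Later treatment, illustration only.** Suppose 30% of an arm relapse by 1 SD. The mean worsens by 0.30 SD and is detected 48% of the time (n = 40, r = 0.5). If half of them are treated again and return to their post-treatment score, the mean shift is 0.15 SD and detection falls to 16%. The article gives no relapse or re-treatment rate.

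**The case against.** A reader might infer that the trial will declare durability whenever p exceeds 0.05. The text does not go that far. The sentence is one of several predictions, beside those on the interaction and on effect sizes, and it is not tied to a decision. Estimated marginal means at each time point, within-group effect sizes and diagnosis-free status are also planned, and the Background hypothesis extends clinically significant improvement to follow-up. A real loss could show in these whatever a test says. This objection stands, but none of these read-outs comes with a criterion for calling the effect maintained.

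A reader might also infer that the TCRF will go unused, or that the design cannot separate lasting benefit from later care. The first rests on the silence of a condensed article, since the full protocol or an analysis plan may give the form a role. The second is wrong about the design, because the data are collected. What can be said is that the analysis as printed does not make the separation.

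It would likewise go too far to say that patients will move from MCT to ERP, or that relapse treated again is scored as success. ERP is usual care at the centre, but the article describes no such pathway and no rate.

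Finally, analysing all observed scores regardless of later care is a legitimate treatment-policy choice. Replacing it with a composite would be a change of question, not the correction of an error.

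**Conclusion.** The point holds in a limited form. The article gives the 30-month visit the purpose of answering durability, but its only stated expectation for change after treatment is non-significance, without a margin or interval criterion. At about 40 evaluable per arm, a true worsening of 0.3 SD would match that expectation in roughly 52% to 66% of trials, so a non-significant result cannot support maintenance. All available follow-up scores also enter whatever later treatment was received, and the printed analysis gives the recorded treatment no role.

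The figures rest on the plan's correlation of 0.5 or its two-step AR(1) counterpart, on 20% drop-out, and on assumed sizes of worsening. Relapse and re-treatment rates are assumptions. The primary post-treatment comparison and the sample size are not affected. The change is worth making because it settles what the trial can conclude on a question it set itself.

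**What to change.** 1. Base the durability statement on the estimated change from post-test to 6 and to 30 months in each arm, with its 95% CI, read against a margin fixed in advance and justified. State that p > 0.05 is not evidence of maintenance. If the margin chosen is tighter than about 0.44 to 0.54 SD, say that the planned size may well leave the question open.
2. Keep the all-observed-data analysis as the main durability result. Beside it, report by arm a supportive analysis using the TCRF: the share recovered at each follow-up with no new or stepped-up OCD treatment since post-treatment. State that the existing recovery criteria are applied to the follow-up score for this purpose.

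The cost is analysis wording only. The data are already being collected, and recruitment was still open when the article appeared. The downsides are that the durability claim becomes harder to meet and that recall on the TCRF, over up to 24 months between the two follow-ups, is imperfect. The second is a reason to keep that analysis supportive.
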